## Abstract

**Background:**

Mosquito-proofing homes was one of the principal methods of environmental management in the early 1900s. House screening provides protection against malaria by reducing exposure to malaria parasites and has the added benefit of protecting everyone sleeping in the house, avoiding issues of inequity within the household. The aim of this study is to determine whether house screening protects people against malaria in Africa. It is hoped that this study will mark the beginning of a series of trials assessing a range of environmental interventions for malaria control in Africa.

**Design:**

A 3-armed randomised-controlled trial will be conducted in and around Farafenni town in The Gambia, West Africa, to assess whether screening windows, doors and closing eaves or installing netting ceilings in local houses can substantially reduce malaria transmission and anaemia compared to homes with no screening. Eligible houses will be sorted and stratified by location and the number of children in each house, then randomly allocated to the interventions in blocks of 5 houses (2 with full screening, 2 with screened ceilings and 1 control house without screening). Risk of malaria transmission will be assessed in each house by routine collections of mosquitoes using light traps and an anaemia prevalence study in children at the end of the main transmission period.

**Discussion:**

Practical issues concerning intervention implementation, as well as the potential benefits and risks of the study, are discussed.

**Trial Registration:**

ISRCTN51184253 – Screening-homes to prevent malaria

## Background

Malaria remains one of the greatest childhood killers in the world[1] and is a substantial obstacle to social and economic development[2]. We know from historical accounts that in the early 1900s malaria was controlled using environmental management (EM) for vector control in many parts of the tropics [3-5]. EM was effective and sustainable in controlling and eradicating malaria, but was forgotten during the DDT campaigns of the 1950s and 1960s. Today most control tools rely exclusively on chemicals (anti-malarial drugs and insecticides), not on environmental modifications, nor on strengthened social systems to perform effective environmental manipulation. Whilst drugs and insecticides are extremely effective weapons, their initial promise has been compromised by the development of resistance [6-10] and growing concerns about long-term environmental impacts[11]. It is therefore of considerable strategic importance to reduce our dependency on antimalarials and insecticides by developing effective and sustainable methods of control. EM could help achieve this and provides new opportunities for the control of malaria that could be incorporated into integrated disease control programmes, providing a more effective, environmentally friendly and sustainable approach to malaria control.

Mosquito-proofing homes was one of the principal methods of EM in the early 1900s (Fig 1) and it should be effective against malaria in Africa since the majority of people receive infective bites at night indoors.

**Figure 1 F1:**
[figure not shown]
A screened entrance to a thatched house in rural Italy in 1900, in an experiment where screening reduced malaria by 96% [20]. This illustrates that even extremely poor housing can be protected from mosquitoes.

The literature review of Lindsay *et *al. provides compelling evidence that house screening has been associated with protection against malaria transmission, infection and morbidity[12]. Furthermore, a pilot study conducted in The Gambia using experimental huts demonstrated that netting ceilings alone can reduce exposure to malaria vectors by 80%[13]. In this situation, most mosquitoes entered the huts through the open eaves and were effectively trapped in the roof space. Further studies in actual village houses are needed to confirm these findings and to assess the acceptability of the intervention to house-holders.

## Methods

### Study area, house- and participant eligibility

The study area is situated approximately 170 km from the mouth of the Gambia River and covers 70 km^2 ^of the North Bank Division in The Gambia, an area of open Sudan savanna vegetation. The climate consists of a single rainy season from June to October followed by a long dry season. Specifically, the study area comprises 500 houses; 46 in 11 residential blocks in Farafenni town (UTM coordinates: 1500200N, 435500E) and 454 in 25 villages located within 15 km of the town. Farafenni itself is a market town with a population of over 20,000 inhabitants, situated less than 5 km from the river and 2 km south of the border with Senegal. Houses in both the town and surrounding villages are usually arranged in familial compounds demarcated by a fence or wall, though there are some in which the houses are rented by unrelated family groups. Compounds in Farafenni contain typically 1–4 houses and in the villages 4–6 houses, but sometimes as many as 20. Houses must meet 6 eligibility criteria in order to be selected: (1) they must be single storey buildings, (2) have open eaves, (3) with no more than four rooms, (4) have no existing ceilings, (5) have no screening and (6) at least one child, aged 6 months to 10 years, must sleep in the house at night. Most of the houses to choose from are part of the Farafenni demographic surveillance system (FDSS) that incorporates 46 residential blocks in the town and 23 surrounding villages, also defined as individual blocks within the FDSS.

The study area population comprises 7852 people dominated by three ethnic groups; Mandinka (28%), Wollof (38%) and Fula (27%). There are roughly equal numbers of men (53%) and women. The study aims to recruit 1250 children aged 6 months to 10 years, as this is the age group most affected by the clinical manifestations of malaria. No distinctions are made regarding gender or ethnic group. Moreover, as the target population will in reality be all children occupying study houses, and in order for the results from this study to be broadly applicable, no distinctions are made in terms of medical condition or physical health.

### Sensitization

Village meetings will be held to explain to the villagers the purpose of the study and the benefit they will receive from participation in the trial. Each meeting will end with an opportunity for asking and answering questions. Informed verbal and written consent is sought from the parents or guardians of children who fulfil the entry criteria for the study.

### Design

In each of 2 intervention years we will erect; full screening on the door(s) and windows and close the eaves with a mixture of sand, rubble and cement (as is normal local practice) in 100 houses and install screened ceilings in a further 100 houses. 50 houses without any screening will serve as a control group. Thus we will enroll a total of 500 houses over the 2 year study. Screening will be installed prior to the rainy season of each year (January to May). All rooms in the house will be screened, not just the target bedroom(s).

Exposure to mosquitoes will be measured by routine surveillance with light traps, fitted near a participant sleeping under an untreated bednet. All children sleeping in eligible houses will sleep under an untreated bednet and their exposure to malaria parasites estimated by (1) haemoglobin density (Hb), (2) percentage of children with anaemia (<8 g/dL), (3) percentage of children with severe anaemia (<5 g/dL), (4) parasite prevalence and (5) high parasite prevalence (> = 5000 parasites/μl), as determined by a cross-sectional survey at the end of the transmission season. At the end of the trial the participants in the control group will be able to choose to have their houses screened, and participants in either of the screening groups will be able to choose to keep that screening, have it removed, or have it changed to the other type of screening. In addition, insecticide-treated nets (ITN) will be provided to all study subjects at the end of the trial.

### Interventions

#### a) Full Screening arm

Door frames will be made from 50 × 50 mm softwood. The doors themselves will be constructed from 15 × 30 mm softwood, strengthened at the corners. Sheets of white PVC-coated fibreglass netting (Vestergaard Frandsen group, Denmark) will be stretched and stapled over the doors (Fig 2a). All doors will open inwards and will be hung on the inside of any existing doors, unless prevented from doing so by an immovable obstruction. Handles and push bars will be fitted on both sides of the door and a catch fixed on the inside to hold the door tight in the frame when shut. Elastic cord will be attached to the outside of the door to pull the door closed when not in use. Windows will be made in a similar fashion to the doors. If the occupants do not need to open the window the netting will be stapled straight onto the 50 × 50 mm frame. If there is already a window in place then the screened window will be installed to the inside of the existing window, and a sliding plywood panel fitted to enable access to the outer window (Fig 2b). Eaves will be closed with a mixture of sand, rubble and cement (Fig 2c).

**Figure 2 F2:**
[figure not shown]
Installation of full screening intervention: a) screened door, b) screened window, c) closed eaves.

#### b) Netting ceiling arm

Sheets of 2.4 m wide white PVC-coated fibreglass netting (Vestergaard Frandsen group, Denmark) will be cut to fit the room (leaving at least 50 cm overhang on all sides), over-lapped and stitched together with ribbon by a local tailor. The netting will be centered over a plywood ceiling rose which is tied by wire to a ceiling beam in the centre of the room (Fig 3a,b). The overhang of the netting will be tucked behind 10 × 40 mm softwood battens which will then be screwed securely to the top of the walls (Fig 3c).

**Figure 3 F3:**
[figure not shown]
Installation of netting ceiling intervention: a) assessing rose height, b) installing ceiling and rose, c) installing battens.

#### c) Control arm

Control houses receive no screening of any type and the eaves remain open.

### Mosquito collection

Each study house will be sampled biweekly during the rainy season. A CDC miniature light trap (Model 512, John W. Hock Co., Gainesville, FL) will be positioned 1 m above the ground within 1–2 m of the foot end of a bed protected with a new untreated bednet provided on that night only. If the trapping room contains multiple beds, then the other room occupants will be encouraged to use their existing bednets. If they have none, additional new bednets will be provided for that night. Light traps will be operated from 19:00 to 07:00 h the following morning. Mosquitoes will be killed by freezing at -25°C for 2 hours and identified using morphological criteria. 1% of the *An. gambiae s.l*. complex caught in the traps will be identified to species by PCR analysis

### Clinical data collection and patient treatment

All children older than 6 months and under the age of 10 years living in eligible houses in the study blocks will be will be issued with an identity (ID) card, which they will present for their correct identification in November at the time of finger-pricking. Axillary temperature will be measured on arrival at the clinical station. A rapid dipstick test (ICT malaria P.f Cassette Test, ICT Diagnostics, South Africa) will be done for any child presenting with temperature ≥ 37.5°C and/or history of fever in the last 48 h. A blood sample will be taken from all children to measure haemoglobin using a portable β-haemoglobin photometer (Hemocue^®^, Ängelholm, Sweden).

In addition, using blood from the same finger-prick, the nurse will make a thin and thick film for confirmation and quantification of malaria parasites. Slides will be numbered with the date of finger-pricking and the subject's randomly generated ID number, and transported to MRC Laboratories Field Station, at Farafenni. Thick blood films will be stained with Giemsa and examined under 1000-fold magnification. Parasite counts will be counted per high power field and 50 fields counted before a slide is declared negative. Parasite density per μL was calculated assuming a blood volume per HPF of 0.002 μL. Thin films will be stained in the field with Field's stain of water-based Romanovsky. *Plasmodium *species will be identified from thin films.

Children with Hb < 8 g/dL will be classified as anaemic and given iron supplementation. Chloroquine and Fansidar will be given to any child ICT-positive, and also to children who were ICT-negative or not tested but were subsequently blood-slide positive. The parents of any child treated for malaria will be asked to bring their child to the nearest Maternal and Child Health clinic if the child is sick and does not recover within 48 h. Children with Hb <5 g/dL will be taken to the Farafenni hospital and followed up for two weeks after fingerpricking.

Clinical data will be recorded initially on the appropriate forms, double entered into a computer by two separate data entry clerks using Microsoft Access 2000, verified and errors amended where appropriate. The original clinical data will be kept in a locked cabinet and the key kept by the local investigator. The digitized dataset will be kept in a server, password protected and only accessed by the data manager and PI at the MRC Laboratories in Farafenni, and the data manager at the central MRC site in Fajara. Data will be stored for at least 10 years.

Thus in a three arm trial we required 200 houses randomized in each intervention group and 100 in the control arm, allowing for 10% of houses to be excluded from the primary analysis due to withdrawal or non-adherence to protocol.

#### b) Clinical

Our aim was to have 90% power to detect a difference in mean haemoglobin of 0.5 g/dl between the two intervention arms and the control arm in November, using a significance level of 2.5% for each of the two comparisons of intervention with control. In a recent trial in The Gambia the SD was 1.7 g/dl. A difference of 0.5 g/dl is 0.3SD. The interclass correlation (ICC) for haemoglobin in another trial in Senegal varied from 0.04 to 0.08. Assuming a similar ICC in the present trial the number of children required to detect (with 90% power) a difference of 0.5 g/dl is 166 in the control arm and 332 in each intervention arm.

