#### d) Primary analysis of variables

##### Entomological data

Comparisons of mean number of mosquitoes/house between intervention groups and the control group will be made using ANOVA on the log mean catch for each house. The mean will be calculated firstly as the Williams mean (geometric mean after adding 1 to all values), and in a secondary analysis, as the arithmetic mean. To allow for the 2 comparisons being made (between the control arm and each of the two interventions), P-values less than 0.025 will be considered significant and 97.5% confidence intervals will be calculated. For the comparison between the two intervention groups, we will estimate the 95% confidence interval for the ratio of the mean catch per house. If the upper limit of this interval corresponds to a difference in catch of 2.5 or less, the ceiling intervention will be considered as effective as full screening.

Estimates of entomological inoculation rate (EIR) will be generated by multiplying the mean number of mosquitoes/adult/house/night by the sporozoite rate (adjusted for area and year) and multiplying this by the number of nights during each year. The sporozoite rate, with a 95% confidence interval, will be estimated for each arm of the trial based on the number of positive and negative pools and the number of individuals per pool, and a confidence interval for the difference between trial arms will be estimated for each pairwise comparison.

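### The haemoglobin sample size of 166/332 children gives 80% power, not the stated 90%, and about 75–78% once the quoted ICC is applied

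*Protocol article*

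**What the plan says.** The section Sample Size Rationale, b) Clinical, sets the target: "Our aim was to have 90% power to detect a difference in mean haemoglobin of 0.5 g/dl", comparing the intervention arms with control in November, "using a significance level of 2.5% for each of the two comparisons of intervention with control". Its inputs are:

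- SD: "In a recent trial in The Gambia the SD was 1.7 g/dl".
- Standardised effect: "A difference of 0.5 g/dl is 0.3SD".
- Clustering: "The interclass correlation (ICC) for haemoglobin in another trial in Senegal varied from 0.04 to 0.08". The text says a similar ICC was assumed for this trial.

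It concludes that the number of children required is, "with 90% power) a difference of 0.5 g/dl is 166 in the control arm and 332 in each intervention arm".

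The paragraph states neither the number of children per house nor whether the test is one- or two-sided. Two other places bear on these. The section on study area and eligibility says "The study aims to recruit 1250 children aged 6 months to 10 years", and the Design section plans 500 houses. The primary entomological analysis handles its two comparisons with control thus: "P-values less than 0.025 will be considered significant and 97.5% confidence intervals will be calculated".

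**The concern.** The inputs and the result are printed together and do not agree. The figure looks like the answer to a different calculation: 80% power with no allowance for clustering. It is presented as 90% power with the ICC taken into account.

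Mean haemoglobin is the clinical outcome in the primary analysis, and this paragraph is its only sample-size justification. A reader would conclude that 166 sampled control children preserve 90% power. Set against the roughly 250 control children the plan implies, that suggests a margin for loss of 84/250 = 34%. The margin matters here. Analysis is limited to children sampled in November, and the Discussion describes a mobile population whose children are often sent away for schooling or weaning.

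**Working it through.** **Inputs.** Difference 0.5 g/dl, SD 1.7 g/dl, alpha 0.025 per comparison, power 90%, ICC 0.04–0.08 and 166 control : 332 per intervention arm (ratio 1:2) all come from b) Clinical. Two inputs are inferred:

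- Two-sided test: the 2.5% is 5% split over two comparisons, and the entomological analysis pairs P < 0.025 with 97.5% intervals.
- Mean cluster size: 1250 children / 500 houses = 2.5.

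**Step 1: try to reproduce the stated figure (no clustering).** With 1:2 allocation,

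n(control) = (z₀.₉₈₇₅ + z_power)² × SD² × (1 + 1/2) / difference²

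- 90% power: (2.241 + 1.282)² = 12.41, and 12.41 × 2.89 × 1.5 / 0.25 = 215.2. That is 216 control and 432 per intervention arm (217/434 by the noncentral t).
- 80% power: (2.241 + 0.842)² = 9.505, and 9.505 × 2.89 × 1.5 / 0.25 = 164.8. That is 165/330 (166/332 by the noncentral t).

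The stated 166/332 is not reproduced at 90%. It is exactly the t-based answer at 80%: power is 79.8% at 165/330 and 80.1% at 166/332.

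**Step 2: add the ICC that the text says was assumed.** Design effect = 1 + (2.5 − 1) × ICC = 1.06 (ICC 0.04) to 1.12 (ICC 0.08).

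- Control children needed for 90%: 215.2 × 1.06 = 228.1 and 215.2 × 1.12 = 241.0, so about 228/456 to 241/482. Starting from the t-based 217 gives 230 to 243 in control.
- Power at 166/332 (normal approximation): 77.8% at ICC 0.04 and 75.2% at ICC 0.08.

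**Step 3: other readings of the inputs, at 166/332.**

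| Reading | No clustering | ICC 0.04 to 0.08, 2.5 per house |
|---|---|---|
| Two-sided 2.5%, 0.5/1.7 | 80% | 77.8% to 75.2% |
| Two-sided 2.5%, rounded 0.3 SD | 82% | 79.5% to 77.1% |
| One-sided 2.5% (same as two-sided 5%), 0.5/1.7 | 87% | 85% to 83% |
| One-sided 2.5%, rounded 0.3 SD | 88% | 86% to 85% |

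None reaches 90%. With the rounded 0.3 SD, a two-sided test still needs 207 control children before clustering.

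**Step 4: what the planned recruitment delivers.** 1250 children split 1:2:2 is 250/500/500. Two-sided 2.5%, 2.5 children per house, ICC 0.04 to 0.08:

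| Children sampled (control / each intervention) | Power |
|---|---|
| 250/500 (no loss) | 92.6% to 91.1% |
| 225/450 (10% loss) | 89.6% to 87.8% |
| 200/400 (20% loss) | 85% to 83% |

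The true margin for loss in control is (250 − 228)/250 = 9% at ICC 0.04 and (250 − 241)/250 = 4% at ICC 0.08, against the apparent 34%.

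**The case against.** The strongest reply is that the figure does not drive the design. House numbers come from the entomological calculation (181 per intervention arm, raised to 200/200/100), recruitment is set at 1250 children, and all eligible children in study houses are to be sampled. At full follow-up the 90% aim is met. This stands: no enrolment, allocation or analysis has to change. The stated requirement and its power are still wrong for an outcome in the primary analysis.

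Second, 75–78% rests on 2.5 children per house. If only 166 control children were sampled across all 100 control houses, the mean would be 1.66 per house, the design effect 1.03–1.05 and power about 78–79%. The point is fair, and the range should carry its assumption. It does not bring power near 90%, and any positive ICC with more than one child per house takes it below the unclustered 80%.

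Third, the paragraph does not state sidedness. A one-sided 2.5% test would give 87% before clustering. That still misses 90%, and the article says so explicitly where it does intend a one-sided test, in the entomological calculation.

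Fourth, the origin of 166 is not established. Two other routes come close to it at 90% power: a one-sided 5% test with ICC 0.08 (149 × 1.12 = 167), and both intervention arms pooled against control at two-sided 5% with ICC 0.06 (152 × 1.09 = 166). Both contradict the stated 2.5% for each of two comparisons. The 80%-without-ICC explanation is therefore the likeliest, not a proven one, and the error does not depend on it.

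Last, the article itself claims no 34% margin. That is what a reader would infer by comparing 166 with 250.

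**Conclusion.** The statement is wrong as written. At the stated 2.5% per comparison, no reading of the printed inputs gives 90% power with 166/332 children. On the natural two-sided reading, power is 80% with independent children. It is about 75–78% with the quoted ICC at 2.5 children per house, and about 74–79% over 1.66 to 3 children per house. The type II error at 0.5 g/dl is about 22–25%, where 10% is claimed.

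The practical harm is limited. Planned recruitment gives 91–93% power with no loss, but the 90% aim holds only if no more than about 4–9% of control children are lost, with proportionate loss in the other arms. These figures assume a two-sided test, the equal SD of 1.7 in all arms and the inferred cluster size. The failure to reach 90% depends on neither the sidedness nor the cluster size.

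**What to change.** In Sample Size Rationale, b) Clinical:

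1. Replace 166/332 by about 228 control and 456 per intervention arm (ICC 0.04) to 241 and 482 (ICC 0.08), defined as children sampled in November. Show the inputs: two-sided 2.5% per comparison, SD 1.7 g/dl, 2.5 children per house and a design effect of 1.06–1.12.
2. If 166/332 is kept, state its power as about 75–78% under those assumptions.
3. Add the power expected at the planned 250/500 after realistic losses, for example about 88–90% with 10% loss and 83–85% with 20%.

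The cost is a corrected paragraph and a less favourable stated margin for loss. No extra enrolment is needed, because 1250 children are already planned.

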### Analysis

#### a) Trial profile

All children in the study will be described in a flow chart and/or the text to indicate, for each arm of the trial, the number of children recruited, the number lost to follow up and reasons for loss to follow up, and the number sampled in November.

The trial profile will also show the number of houses considered for enrolment, the number excluded from the study with reasons for exclusion, the number randomized in each group, and the number withdrawn with reasons for withdrawal.

